#### Range of motion reliability study

Due to the novel range of motion testing device employed by researchers at seven test sites in the SHORT Trial, a feasibility and reliability study to determine the reproducibility of measures was deemed necessary. Inter-tester reliability for the standardized methods of obtaining range of motion measures was established by having 10 different measurers of varied experience (medical and non-medical backgrounds) assess each of the motions (scaption, ER (0), ER (90), and IR) on three different subjects. Active and passive range of motion measurements were obtained three times on each subject, and the means of the three active and three passive trials were used to develop a Pearson inter-tester correlation coefficient (ICC) for each motion. For each of the three trials, subjects moved to a pre-determined range of motion, which was either at the beginning of the range, mid-range, or end range in order to ensure reliability throughout range of motion. Variability due to subjects moving to different points in the range of motion was minimized by having this pre-determined range of motion; measurers were blinded to the pre-set subject range of motion value. The 10 measurers were provided with a training video explaining how to obtain the measures, a detailed training manual, and clinic cards with measurement method summaries and pictures for use as a reference. These materials are the same used to train all clinical research assistants at each participating center in the study. Examination of the data following the first reliability study revealed that the numbers obtained for ER (90) were not reflections of the true range of motion measured, and there was more variability than desired for ER (0). Measures of ER (90) were not accurate because the Clinometer was not being zeroed at the true horizontal, therefore this step was added to the measurement process. The ER (0) variability was attributed to the goniometer being placed on the top of the subjects’ forearm which created difficulty for accurate alignment of the axis of rotation at the elbow. A change in the method was devised to have subjects rest the arm on top of the goniometer stable arm, which was secured to the custom device, and have the subject place the elbow on the goniometer axis of rotation. Following these changes in ROM methods upon completion of the pilot reliability study, a second reliability trial was conducted in the same manner which revealed that the ICCs were considered to be high, [45] reflecting that these methods can be repeated with reliability across participating study sites: scaption 0.98, ER (0) 0.89, ER (90) 0.69, and the active IR was repeated within 2 measurement levels across all subjects.

#### Secondary outcomes

##### Costs and complications data

Total number of visits to the physical therapist for patients in the PT group, compliance with the therapy plan, and complications are obtained from the medical record and the patient questionnaires (Appendix A). Medicare and private payer physical therapy reimbursement data are obtained through the PearlDiver database. Whilst we recognize that “true cost” is a fluid concept in health care, this information, along with calculation of quality adjusted life years from PROMIS-29 v. 2.0 allows us to perform a cost-effectiveness analysis.

Table 2 lists and defines complications tracked as part of the study. We specifically are assessing for the incidence of acromial or scapular spine stress fractures and shoulder dislocation which may be impacted by the rehabilitation strategy, and therefore will be compared between groups. Additional complications including infection, nerve palsy, or other post-operative events related to surgery (eg. periprosthetic fracture) will not be compared between groups. In addition, any unanticipated presentation to a hospital, urgent care, or physician’s office for any reason is also recorded as an adverse event. All complications and adverse events are reviewed by an independent safety monitor.

**Table 2 Tab2:** Complications tracking chart

Complication	Definition
Acromial or scapular spine stress fracture	Diagnosed clinically with following findings: 1. Sharp pain referred to the acromion/scapular spine worse with deltoid activation; 2. Tenderness with palpation of the acromion/scapular spine.
Dislocation	Radiographically confirmed dislocation of the articulating surfaces.
Infection	“Definite” or “Probable” periprosthetic infection as diagnosed by the ICM criteria [46].
Nerve palsy	Impairment of an ipsilateral upper extremity nerve as detected by loss of sensation or a reduction in motor strength in the distribution of a particular peripheral nerve
Other (related to surgery) Explain	Any other complication related to the study shoulder (eg. prosthetic loosening, mechanical dissociation, periprosthetic fracture)
Other (adverse event, unrelated to surgery) Explain	Unanticipated presentation to a hospital, urgent care, or physician’s office for any reason not categorized above within 90 days post surgery.

Clinical research assistants are not blinded due to the need to facilitate appropriate group assignments therefore they are aware of patient group assignment (PT vs HT). Patients are not blinded to group assignment due to their awareness of the rehabilitation occurring at either a physical therapy clinic in weekly appointments or at routine post-operative appointments with the surgeon. For subjects in the PT group, clinical research assistants arrange physical therapy appointments at the appropriate follow-up and ensures the physical therapist is trained with the protocol. For subjects in the HT group, clinical research assistants facilitate the progression of exercises that are taught by the surgeons at the post-operative standard of care appointments during the first 3 months of follow-up. Surgeons and clinical research assistants are trained in the HT exercise progression provided in the pre-printed exercise sheets. For both groups, clinical research assistants obtain the patient reported outcome measures, range of motion measures, and collect patient data regarding compliance, cost, and complications.

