## Abstract

**Background:**

Reverse total shoulder arthroplasty (RTSA) has emerged as a successful surgery with expanding indications. Outcomes may be influenced by post-operative rehabilitation; however, there is a dearth of research regarding optimal rehabilitation strategy following RTSA. The primary purpose of this study is to compare patient reported and clinical outcomes after RTSA in two groups: in one group rehabilitation is directed by formal, outpatient clinic-based physical therapists (PT group) as compared to a home therapy group, in which patients are instructed in their rehabilitative exercises by surgeons at post-operative appointments (HT group). Secondary aims include comparisons of complications, cost of care and quality of life between the two groups.

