## Discussion

Currently there are two published studies, which prospectively evaluate rehabilitation following RTSA. Hagen et al. have reported results from a randomised controlled blinded study regarding following RTSA assessing early versus delayed mobilization, and conclude that early mobilization is safe, and may offer advantages to the elderly population [31]. Lee et al. reported that not using a sling following RTSA resulted in non-inferior outcomes as compared to sling immobilization for 3 or 6 weeks [32]. Whilst these studies illuminate the potential benefit of an early and accelerated rehabilitation strategy, they do not address the question of how the rehabilitation should be structured, specifically whether formal physical therapy is required or if the rehabilitation can be conducted effectively through a surgeon directed home exercise program. An ideal rehabilitation strategy following RTSA optimizes outcomes while minimizing cost and inconvenience to patients. Thus, the necessity for formal, clinic-based physical therapy should be determined. This study proposes to answer this question with a large prospective, multi-center, randomised controlled trial across several regions of the United States producing generalizable results. If the HT group has the same or better outcomes than the formal PT group, then surgeon-directed home therapy is a convenient and cost-effective rehabilitation strategy for patients who have undergone RTSA. If the PT group has better outcomes without increased harm/complications to patients, then a studied rehabilitation strategy can be endorsed. The prospective and randomised nature of the project are strengths, whilst the cross-over option allows for patient preference and safety.

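### The planned complication comparison covers two event types and expressly bars three others, which is narrower than the harm condition in the Discussion

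*Protocol article*

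**What the plan says.** **Conclusion to be drawn.** The Discussion states: "If the PT group has better outcomes without increased harm/complications to patients, then a studied rehabilitation strategy can be endorsed". It does not limit which harms count.

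**Aim.** The abstract is equally broad: "Secondary aims include comparisons of complications, cost of care and quality of life between the two groups". The main Background narrows this to acromial stress fractures and prosthetic instability, and expects both to be more frequent with PT.

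**Comparison planned.** Under Costs and complications data: "We specifically are assessing for the incidence of acromial or scapular spine stress fractures and shoulder dislocation". The reason given is that rehabilitation may influence these two events. Next comes the exclusion: "Additional complications including infection, nerve palsy, or other post-operative events related to surgery (eg. periprosthetic fracture) will not be compared between groups". The Complications analysis section defines a rate and a chi-square test at p < 0.05. It speaks of the complication generically and does not bring back the excluded events.

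**Other handling.** "All complications and adverse events are reviewed by an independent safety monitor". Unplanned care is also collected: "In addition, any unanticipated presentation to a hospital, urgent care, or physician’s office for any reason is also recorded as an adverse event". The matching row of Table 2 adds a time limit: "for any reason not categorized above within 90 days post surgery".

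**The concern.** The evidence planned on harm is narrower than the statement it is meant to support. If the plan is followed as written, a finding that PT improves outcomes without added harm would rest on two event types. Infection, nerve palsy and the other surgery-related events would be collected in both arms, but the stated rule is that they are not compared. That last group includes loosening, mechanical dissociation and periprosthetic fracture.

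One use of randomised safety data is to reveal harm that nobody predicted, in either arm. Both compared events were hypothesised to be worse with PT. An unexpected excess of some other shoulder complication, in either arm, has no planned place in the conclusion.

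This is an explicit rule in the current text, so it is not a detail that the article has left to an analysis plan.

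**Working it through.** The plan gives no figure on this point, so there is none to reproduce. The check sets the sections side by side, followed by an illustration of scale.

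**1. Status of each Table 2 row**

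| Table 2 row | Related to shoulder or surgery | Between-arm comparison |
|---|---|---|
| Acromial or scapular spine stress fracture | yes | planned |
| Dislocation | yes | planned |
| Infection | yes | expressly barred |
| Nerve palsy | yes | expressly barred |
| Other, related to surgery | yes | expressly barred |
| Other, unrelated adverse event | no | not stated |

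This gives 2 of 6 rows compared, 3 of 6 barred and 1 of 6 silent. Among the five related rows, 3 of 5 are barred.

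**2. Does another section restore the barred events?** The Complications analysis section names no events, so it cannot override an express exclusion. The safety monitor reviews all events, but no comparison by arm and no link to the trial's conclusion is described. Neither closes the gap.

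**3. Scale (illustration only, not predicted rates).** The Sample size section gives enrolment of 182, which is 182 / 2 = 91 per arm under 1:1 allocation. For a events against b events with n per arm, the Pearson chi-square without continuity correction is 2n(a(n − b) − b(n − a))² / [n² (a + b)(2n − a − b)].

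- 0 v 4: 182 × (0 × 87 − 4 × 91)² / (91² × 4 × 178) = 182 × 364² / 5,896,072 = 4.09, p = 0.043. Fisher exact p = 0.121.
- 2 v 9: 182 × (2 × 82 − 9 × 89)² / (91² × 11 × 171) = 182 × 637² / 15,576,561 rounded inputs as shown = 4.74, p = 0.030. Fisher exact p = 0.058.

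Either imbalance in a barred row would meet the plan's own chi-square criterion, yet would not be compared. The Fisher values show how fragile such p-values are with few events. At 100 per arm (the abstract gives 200 subjects) the chi-square results hardly move: 0 v 4 gives p = 0.043 and 2 v 9 gives p = 0.030.

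**4. Would more tests help?** Take a doubling from an assumed rate p₁ to p₂ = 2p₁, where p₁ is my assumption and not in the document. Power = Φ[(Δ − 1.96 SE₀) / SE₁], with Δ = p₂ − p₁, SE₀ = √[2p̄(1 − p̄)/n] where p̄ = (p₁ + p₂)/2, and SE₁ = √[(p₁(1 − p₁) + p₂(1 − p₂))/n].

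- p₁ = 1%: Δ = 0.01, SE₀ = 0.0180, SE₁ = 0.0180, power about 8%.
- p₁ = 5%: Δ = 0.05, SE₀ = 0.0390, SE₁ = 0.0389, power about 25%.

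Extra significance tests would therefore mostly fail to detect a real excess. Estimates with intervals say more. For 2 v 9 at 91 per arm, the risk difference is 9/91 − 2/91 = 7.7 percentage points. Its standard error is √[(0.0220 × 0.9780 + 0.0989 × 0.9011)/91] = 0.0349. The Wald 95% interval is 7.7 ± 1.96 × 3.49, or about 0.9 to 14.5 points.

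**The case against.** The strongest defence is that the restriction is prespecified and reasoned. The two compared events are those that rehabilitation is thought to influence, and confining tests of rare events to stated hypotheses is good practice. The only comparison method the article gives is the chi-square test, so the exclusion may mean only that the other events are not formally tested. A descriptive harms table is something an article often leaves to the full protocol or the report. The first part stands: the two tested endpoints should stay. The second does not settle the matter, because the exclusion is not limited to testing and, read plainly, it rules out any comparison.

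Several stronger readings go beyond the text:

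- A reader might count four of six rows as excluded. Only three are. For unrelated adverse events the article is silent, and with the analysis plan not shown, silence is not a defect.
- A reader might infer that other harms cannot affect the conclusion. The Discussion sentence is not a formal decision rule, and the safety monitor reviews every event. What can be said is that no between-arm route is planned.
- A reader might infer that home therapy will be declared the safe option. The Discussion calls it convenient and cost-effective if outcomes are the same or better. It makes no safety claim for it.
- A reader might infer that the compared harms were picked for their expected direction. The stated criterion is possible influence of rehabilitation, and the chi-square test detects a difference either way.
- Mechanisms such as falls during unsupervised exercise appear nowhere in the article, and both arms follow the same Table 1 guidelines.

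**Conclusion.** The point holds as a mismatch between two statements in the current text. The harm condition in the Discussion and the aim in the abstract are general. The comparison covers two event types and bars three of the five shoulder- or surgery-related rows. The primary analysis is unaffected, but a general statement on harm would not be supported by the comparisons planned.

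The size is best given as this count of categories. The event counts in the illustration are hypothetical and assume 91 per arm. They show only that a visible imbalance could go uncompared, not that one is likely.

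The differing time limits for unanticipated presentations are a separate, minor matter. The text sets no limit and Table 2 sets 90 days, while follow-up runs to two years. The article presents Table 2 as the place where complications are defined, so a reader can probably resolve it, but sites should not have to.

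**What to change.** In Costs and complications data, replace the sentence that bars comparison with wording such as: *Every Table 2 category, and the number of patients with any complication related to the study shoulder, will be tabulated by randomised arm as patients with at least one event, with the risk difference and its 95% confidence interval. These results are descriptive and carry no significance test. Stress fracture and dislocation remain the two tested complication endpoints.*

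Then base the harm statement in the Discussion on that full table. If the sponsor prefers to keep the exclusion, the minimum change is to narrow the Discussion sentence to stress fracture and dislocation.

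State one time window for unanticipated presentations in both the text and Table 2.

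Cost: one table from data already collected and a few changed sentences, with no new visits and no change to the sample size. The downside is more estimates with wide intervals, which must be labelled descriptive so that chance differences are not over-read.

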We aim to compare outcomes for formal, clinic-based physical therapy (PT group) to home therapy, in which patients are provided with instructions from surgeons at post-operative appointments (HT group) by using a superiority, randomised design [34]. Findings will aid in determining the potential role of formal PT in the RTSA recovery process, and secondarily, will evaluate a formal RTSA rehabilitation protocol, which is standardized for the trial [20].. Findings from the study may assist in evaluating the financial benefit or burden of formal PT in the RTSA recovery process and determine the resource necessity of PTs in a traditional clinical environment. We hypothesize that the PT group will demonstrate superior clinical and patient reported outcomes, significantly quicker levels of recovery, and significantly higher levels of overall recovery at our long-term outcomes capture when compared to the HT group. Secondary aims of this project include analysis of the incidence of complications between the two groups, specifically acromial stress fractures and prosthetic instability events, which we hypothesize will be higher in the PT group; and cost of care which we hypothesize will be higher in the PT group.

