##### Physical therapy intervention group

Subjects in the PT group will begin out-patient clinic-based rehabilitation 4–5 days after discharge from the hospital and continue in therapy approximately once a week for three months. Physical therapists will employ a pragmatic approach within the rehabilitation guidelines summarized in Table 1. Physical therapists will determine the optimal exercises for each patient within the specified guidelines for each phase of recovery. The exercises may vary amongst subjects considering patient specific variables such as exercise tolerance and pain response, ease of progressing to next level of challenge, ability to follow directions and perform exercises correctly, and individual goals for rehabilitation. The number of physical therapy visits may vary amongst patients in this group depending on response to therapy. For example, patients with low demand goals for rehabilitation and/or those who tolerate therapy well and advance easily may need less PT visits than patients with high demand goals and/or those who don’t tolerate therapy well and progress more slowly.

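### The stress fracture comparison is open to detection bias towards more events under physical therapy; the size of the bias is unknown

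*Protocol article*

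**What the plan says.** The Background names acromial stress fractures and prosthetic instability as the complications of interest, "which we hypothesize will be higher in the PT group". The section on costs and complications data limits the comparison of arms to two events, stress fracture and dislocation; other complications are recorded but not compared.

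Table 2 sets different standards for the two compared events:

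- Dislocation: "Radiographically confirmed dislocation of the articulating surfaces".
- Stress fracture: "Diagnosed clinically with following findings: 1. Sharp pain referred to the acromion/scapular spine worse with deltoid activation", together with tenderness when that area is pressed. No imaging is part of the definition.

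Under Complications analysis, the number with an event is divided by the number of subjects in the arm, and the arms are compared by a chi-square test at p < 0.05. Events are taken from the medical record and from patient questionnaires. The research assistants who collect them are not blinded.

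The contact schedules differ by design. PT patients start outpatient therapy 4 to 5 days after discharge and "continue in therapy approximately once a week for three months", with the number of visits allowed to vary. Both arms see the surgeon at 2 and 6 weeks, 3 and 6 months, and 1 and 2 years (Eligibility criteria/subjects). HT patients have their exercises advanced at the first three of those visits. The questionnaire is given at every one of these appointments in both arms (Participant timeline). The article also states: "All complications and adverse events are reviewed by an independent safety monitor".

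**The concern.** An event defined by pain and tenderness is counted only if someone notices it and writes it down. For the first three months PT patients have many more occasions on which that can happen. Table 1 makes those occasions relevant: leaving phase 2 requires painless firing of the deltoid, and leaving phase 3 requires absence of pain, so a therapist applying the guidelines will often provoke or ask about the first of the two defining findings. The definition requires neither persistence nor imaging, so short-lived acromial pain seen between surgeon visits can qualify.

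Because every event found by any route goes into the numerator, opportunity for detection is mixed with incidence. An effect of this kind would point the same way as the stated hypothesis for complications. The Discussion says that a rehabilitation strategy could be endorsed if PT gives better outcomes without added harm or complications. An excess of stress fractures due only to closer observation would bear directly on that conclusion.

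**Working it through.** The article gives no contact ratio, no expected stress fracture rate and no detection probability, so there is no stated figure to reproduce. The contact counts come from the article. The risks and detection rates below are assumptions, shown over a range.

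**Step 1. Contacts to three months.** Weekly visits for three months are about 12 to 13. Surgeon visits in that period: 3 in each arm.

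- PT: 12 + 3 = 15 to 13 + 3 = 16. HT: 3.
- Ratio: 15/3 = 5.0 to 16/3 = 5.3. With 10 to 14 therapist visits it is 13/3 = 4.3 to 17/3 = 5.7.
- Over two years, with 6 surgeon visits per arm: (12 + 6)/6 = 3.0 to (13 + 6)/6 = 3.2.

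**Step 2. Missed events in HT.** Let the true risk be the same in both arms, and let HT detection be a fraction r of PT detection. The expected observed rate ratio is 1/r. The probability that an uncorrected chi-square test is significant with PT higher was found by exact enumeration of two binomials with 91 per arm (182/2, from the Sample size section). PT detection is set to 100%.

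| True risk | r = 1.00 | r = 0.90 | r = 0.75 | r = 0.50 |
|---|---|---|---|---|
| Rate ratio 1/r | 1.00 | 1.11 | 1.33 | 2.00 |
| 2% | 1.8% | 2.2% | 2.9% | 4.5% |
| 4% | 2.2% | 2.9% | 4.7% | 10.4% |
| 10% | 2.5% | 4.2% | 8.6% | 24.3% |

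With incomplete detection in both arms at 4% true risk:

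- 90% in PT against 60% in HT gives 0.04 × 0.90 = 3.6% and 0.04 × 0.60 = 2.4%, a ratio of 1.5. Expected events are 91 × 0.036 = 3.3 and 91 × 0.024 = 2.2. The false PT-higher probability is 5.9%.
- 95% against 50% gives 3.8% and 2.0%, a ratio of 1.9, and 9.2%.

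**Step 3. Over-diagnosis.** Let each contact carry a probability f of a false diagnosis in a patient without a fracture, with 15 contacts in PT and 3 in HT. The probability of at least one is 1 − (1 − f)^15 against 1 − (1 − f)^3.

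- f = 0.1%: 1.5% against 0.3%, a gap of 1.2 points.
- f = 0.5%: 7.2% against 1.5%, a gap of 5.8 points before rounding.

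Added to a true risk of 4% (so applied to the other 96%), these widen the difference between arms by 1.1 and 5.5 points. The false PT-higher probability becomes 4.6% and 27.2%.

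**Step 4. What the common visits do.** If every true HT case is still found at the shared surgeon visits or on the questionnaire, r = 1 and Step 2 shows no bias. Those visits do not remove the mechanism in Step 3, because false diagnoses made between visits remain in the count.

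**The case against.** A reader might infer that the complication comparison as a whole is biased against PT. The documents do not support that. Only two events are compared, and dislocation must be confirmed by radiograph. Nor can bias in the stress fracture comparison be called established:

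- Both arms share six surgeon visits and questionnaires to two years, so a persisting fracture in HT has several chances of being found.
- Unanticipated visits to a hospital, urgent care or physician's office are also recorded (within 90 days of surgery for the residual category in Table 2), which gives HT a route between visits.
- No passage makes a therapist's observation a diagnosis. Some PT patients are treated near home by outside therapists, whose notes may never reach the trial's records.
- Both arms follow the same phase guidelines. Active elevation starts only at 6 weeks and deltoid weights at 12 weeks, about when formal therapy ends.
- Staff expectation does not run one way: the primary hypothesis is that PT is superior.

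These points stand. They limit missed events and leave the size unknown. They do not remove over-diagnosis, since the definition needs neither persistence nor imaging, and the safety monitor can review only what has been reported. That the article does not say whether the monitor is masked is not held against it; a condensed article may leave that to the full protocol.

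A reader might also infer that a surveillance excess would overturn a real benefit of PT. That is not shown. The sentence on endorsement is Discussion prose and not a formal decision rule, and in the 90%/60% illustration the arms differ by about one expected event.

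Finally, restricting the main comparison to events found at scheduled visits would drop genuine safety events, probably mostly in PT, and so favour a finding of no difference. That objection is accepted, and the restriction belongs in a sensitivity analysis.

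**Conclusion.** The point holds for stress fracture and not for dislocation. The comparison is open to detection bias towards more events in PT, for three reasons that the article itself states: a definition resting on pain and tenderness, about five times the contacts in the first three months (about three times over two years), and events taken partly from the medical record by staff who know the arm.

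Its size cannot be fixed from the documents. Across the assumed 2% to 10% risks and HT detection of 50% to 90% of PT, the chance of a false significant PT excess runs from 2.2% to 24.3%, against about 2% to 2.5% without bias. At 4% risk under the two incomplete-detection settings it is about 6% to 9%. It could also be nil for missed events if the common visits find every HT case. This is a secondary outcome with few expected events, so the matter warrants an inexpensive safeguard and does not call the design into question.

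**What to change.** 1. Keep all events meeting Table 2 in the stated comparison of arms.
2. Record for each event how it was first detected: scheduled visit, therapist referral, or patient-initiated contact.
3. Prespecify a sensitivity analysis restricted to stress fractures present or reported at the common scheduled visits (2 and 6 weeks, 3, 6, 12 and 24 months).
4. Have the existing independent safety monitor classify stress fracture cases against Table 2 from summaries with arm and therapy contacts removed.
5. State that an excess in PT will not be read as harm from therapy unless it persists in the common-visit analysis. Judge this on the estimate and its confidence interval, since a significance test on so few events says little.

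The cost is one form field, masked case summaries for a reviewer already in place, and a few lines of analysis text. No definition, treatment or visit changes. There are limits. The sensitivity analysis will rest on few events. Masked classification addresses over-diagnosis but cannot recover HT cases that were never noticed. A PT patient alerted by a therapist may still be more likely to report pain at the next common visit.
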